### ***Exclusion Criteria***

The exclusion criteria of the MULBERRY trial are listed in table 1.

In addition, participants will be excluded if they are unable to comply with experimental procedures or do not follow GR and IR testing safety guidelines.

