### ***Suspension Criteria***

All adverse events will be monitored and recorded from the time of the screening visit through 24 hours after treatment visit. Subjects may be excluded or have the study product discontinued if the investigator decides discontinuation of the study product is in the best medical interest of the subject (e.g., due to noncompliance, changes in medications or dietary supplements, an adverse event or serious adverse event, or a change in medical status) or if the subject requests withdrawal from the study.

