### ***Sample Size***

A recent study in India (which is yet to be published) in 12 healthy individuals age 18-25 using 250mg ME dose showed a reduction in the glycaemic index of maltodextrin by 58% when compared to placebo. A sample size of 30 would allow over 90% power to detect a difference of a similar size. Being more conservative and allowing for a smaller difference to be detected in the lower concentration doses, 30 participants would still allow at least 80% power to detect a difference of 25% in the incremental Area Under the Curve (iAUC). In order to account for a potential loss to follow up, and the possibility that our sample size may be inaccurate as it is based on a small pilot sample we will therefore recruit 40 participants.

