## ***Statistical Analysis***

This is the first rigorous study of IM and should therefore be considered as a pilot study from a statistical perspective. We will calculate the incremental area under the curve for all 4 study products and compare using repeated measures ANOVA to determine whether there is a statistically significant difference in plasma glucose levels and in secondary outcome measure over the 120 minute period. All models will control for the possible confounding effects of sex and BMI. The presence/absence of gastrointestinal symptoms in the 24 hours following the study visit will be assessed using logistic regression models. We anticipate a low likelihood of missing data (as sufficient blood is taken for a second analysis to be performed if the first analysis fails) and our glucose values will be measured in real time. We anticipate monophasic or biphasic glucose and insulin curve responses and will use a 2nd order interpolation method for missing data, provided that no other data is missing from the two neighbouring time points at either side of a missing data set and that the baseline and end data values are obtained. If the baseline or end points are missing or more than one data point within five neighbouring time points, this data set will be deemed unsuitable and not be included in the analysis.

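### Incomplete curves are deleted and iAUC is then compared by repeated measures ANOVA, which in its classical form also discards the affected participant's other valid curves for that analyte

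*Protocol*

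**What the plan says.** The Protocol's Study Design section has every participant test all four products, so a complete participant supplies four glucose curves and four insulin curves.

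The Statistical Analysis section fixes two things. First, iAUC is compared across the products by repeated measures ANOVA, with adjustment for sex and BMI. Second, a curve is removed when its baseline or end value is missing, or when more than one value is missing within five neighbouring time points: "this data set will be deemed unsuitable and not be included in the analysis". Other single gaps may be interpolated. The section does not say what happens to the same participant's remaining curves. It expects little missing data, because enough blood is drawn for a repeat analysis and glucose is read in real time.

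The Sample Size section bases its power statements on 30 participants. It first cites a pilot that "showed a reduction in the glycaemic index of maltodextrin by 58% when compared to placebo" and says "A sample size of 30 would allow over 90% power to detect a difference of a similar size". It then says "30 participants would still allow at least 80% power to detect a difference of 25" per cent in iAUC. The margin is explained by "In order to account for a potential loss to follow up" and by possible inaccuracy of the calculation: "we will therefore recruit 40 participants".

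Participants can also leave after randomisation. Suspension Criteria says "Subjects may be excluded or have the study product discontinued", and Exclusion Criteria says "participants will be excluded if they are unable to comply with experimental procedures". Neither section says whether visits already completed stay in the analysis.

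**The concern.** Each rule is understandable alone, but together they waste data. A lost 120-minute sample cannot be interpolated, so that visit's curve goes. Classical repeated measures ANOVA needs a full set of four iAUC values per person, so the participant's three good curves for that analyte go too. A missed visit has the same effect.

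In a crossover this is avoidable. A participant with placebo and two doses still gives a within-person contrast for both of those doses. Discarding those contrasts costs precision, and it draws on a reserve that is also meant to cover an inaccurate sample size calculation. It also confines the primary comparison to participants who completed everything.

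**Working it through.** **Inputs from the Protocol.** 40 recruited and 30 behind the power statements (Sample Size); four curves per participant for each analyte (Study Design); the deletion rule and the named method (Statistical Analysis).

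**Inputs assumed.** The loss rate per curve, *q*, is not given, so a range of 2% to 10% is shown. Losses are taken as independent across curves. The SD of the within-person difference, alpha and sidedness are not given either.

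**The plan's own figures.** The reserve reproduces as 30 / (1 − 0.25) = 40, so it covers a loss of one participant in four. The stated power cannot be reproduced without an SD and alpha. Working backwards with a paired t-test at two-sided 0.05, 80% power at n = 30 for a 25% difference needs a standardised difference of 0.529. That implies a within-person SD of 25 / 0.529 ≈ 47% of the placebo iAUC. With that SD, power for a 58% difference exceeds 99.9%, so the two power statements are compatible.

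**When the reserve runs out under complete-case analysis.**
- The number with complete sets falls below 30 once 11 of 40 participants have at least one unusable curve or missed visit (40 − 11 = 29). If each loss falls in a different person, that is 11 / 160 = 6.9% of curves.
- In expectation, 40(1 − q)⁴ = 30 gives q = 1 − 0.75^(1/4) = 6.9%.

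**Complete sets against all usable curves.** Expected complete sets are 40(1 − q)⁴. Participants with both curves of one dose-placebo pair number 40(1 − q)². This is a lower bound on what a mixed model uses, because it also draws information from incomplete pairs. Usable curves thrown away are 160(1 − q) − 160(1 − q)⁴.

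| q | Complete sets | Pairs kept per comparison | Usable curves | Of these, discarded |
|---|---|---|---|---|
| 2% | 36.9 | 38.4 | 156.8 | 9.2 |
| 5% | 32.6 | 36.1 | 152.0 | 21.7 |
| 7% | 29.9 | 34.6 | 148.8 | 29.1 |
| 10% | 26.2 | 32.4 | 144.0 | 39.0 |

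**Chance of fewer than 30** (binomial, 40 participants):
- Complete sets: 0.02% at q = 2%, 0.4% at 3%, 11% at 5%, 52% at 7.5% and 86% at 10%.
- Pairs kept: 0.1% at 5%, 2.3% at 7.5% and 12% at 10%.

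**What this means for power** at the implied SD of 47%: 90% at n = 40, 87% at 36, 83% at 32, 80% at 30 and 74% at 26. At 5% loss the two approaches therefore sit at roughly 83% and 87%. At 10% they sit at roughly 74% and 83%.

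**The case against.** The strongest reply is that the Protocol never says a participant is dropped. It removes one data set, and some forms of repeated measures analysis keep the rest. The handling of incomplete sets may also be set out in an SAP that is not at hand. This is right about the wording: participant-level deletion is inferred from the usual form of the named method. But the Protocol itself fixes the method and the deletion rule, and the plain reading of the two together is wasteful.

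The second reply is that little loss is expected. Blood is drawn for a repeat analysis, glucose is read at once, and ten participants are held in reserve. At 2% or 3% loss the sample stays above 30 almost surely. This largely stands. It has one limit: spare blood rescues a failed assay, not a missed visit or a sample never taken. Independence also tends to overstate the problem, because withdrawal concentrates missed visits in the same people.

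A reader might infer four stronger things that the document does not support.
- **That one loss removes the participant from every analysis.** A lost insulin curve need not remove the glucose curves, and gastrointestinal symptoms are analysed separately by logistic regression.
- **That the analysed sample will fall below 30.** This needs 11 of 40 participants affected, and nothing in the Protocol suggests so many.
- **That people who tolerate a higher dose poorly will be selectively removed.** Exclusion Criteria and Suspension Criteria allow exclusion, but neither says completed visits are discarded. Product-related selection is a risk, not something shown.
- **That the interpolation rule fails at 15 and 90 minutes.** The −5 and 0 minute samples both precede 15 minutes, and a single lost 90-minute value does not trigger the deletion sentence. The wording is at most a minor clarification.

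**Conclusion.** The point holds in a limited form. Read with the classical form of the named method, the Protocol's rules discard up to three valid curves per affected participant for that analyte. The size depends on a loss rate the Protocol does not give. It is about 9 of 157 usable curves at 2% and 22 of 152 at 5%, and the 40-to-30 reserve is used up at about 7% per curve. At the low missingness the Protocol expects, the consequence is some loss of precision. These figures rest on independent losses, and the power figures also rest on a back-calculated SD and a two-sided 0.05 test. The change is worth making because a better method costs almost nothing, not because the trial is shown to be underpowered or biased.

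**What to change.** In Statistical Analysis, replace repeated measures ANOVA with a linear mixed model for iAUC, with participant as a random effect, product and period as fixed effects, and sex and BMI as already planned. Fit it to every usable visit curve, separately for glucose and insulin.

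State that the deletion rule removes the single curve only. State also that the completed visits of participants who withdraw or are excluded stay in the analysis. Report complete-case repeated measures ANOVA as a sensitivity analysis. While the text is open, one sentence could confirm how a single missing 15- or 90-minute value is interpolated.

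The cost is a change of wording and slightly more analysis work, with no new data. The mixed model assumes losses are missing at random, which should be said. Trial Status reports that recruitment has finished and most participants have completed all visits, so the change should be fixed and dated before the randomisation code is opened.

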## **Discussion**

In this paper, we have suggested the clinical trial design of a dietary supplement to reduce glucose excursions without a disproportionate increase in insulin release. This pilot study will influence further work on a larger scale RCT. In this study we aim to confirm the standard dose of IminoNorm that can be consumed with food. In addition, we aim to determine the magnitude of clinical effect and to measure the frequency and intensity of any gastrointestinal side effects. Based on the results, we will aim to design a larger RCT to investigate the protective effect of ME on the development of pre-diabetes and diabetes in at risk individuals or the population as a whole. The treatment effect size may be used to determine the sample size of a larger study based on similar studies on the prevention of T2DM As mentioned previously, ME may also have a positive effect on lipid profiles and we may decide to include further endpoints in future larger trials. Glucose-lowering agents show ethnic variations and future work should include assessment in more ethnically diverse populations.

## **Trial Status**

We have now finished recruiting and most of the participants have completed all 4 visits.

## **List of Abbreviations**

ME: Mulberry Extract, T2DM: Type 2 Diabetes Mellitus, BMI: Body Mass Index, TCM: Tradition Chinese Medicine, DNJ: 1-deoxynojirimycin, GR: Glycaemic Response, IR: Insulinaemic Response, UREC: University Research Ethics Committee, iAUC: Integral Area Under the Curve, GCP: Good Clinical Practice, ANOVA: Analysis of Variance, RCT: Randomised Controlled Trial.

## Competing Interests

The authors are funded by a Technology Strategy Board / Innovate UK grant to undertake this work with Phynova (as the applicant) and our role is solely that of researchers

## Acknowledgements

The work has been funded by a Technology Strategy Board/Innovate UK grant.

## **Additional File**

An additional file has been included which details recommended items to address in a clinical trial protocol and related documents.

**Table 1 Exclusion criteria of the Mulberry trial**

| Exclusion Criteria                                                                                                                             |
|------------------------------------------------------------------------------------------------------------------------------------------------|
| 1. Aged < 18 or > 60 years                                                                                                                     |
| 2. Pregnant or lactating                                                                                                                       |
| 3. Body mass index (BMI) < 20kg/m  and > 30kg/m                                                                        |
| 4. Fasting blood glucose value > 6.1 mmol/l                                                                                                    |
| 5. Any known food allergy or intolerance including mulberry extract                                                                            |
| 6. Medical condition(s) or medication(s) known to affect glucose regulation or appetite and/or influence digestion and absorption of nutrients |
| 7. Known history of diabetes mellitus (Type I/II) or the use of antihyperglycaemic drugs or insulin to treat diabetes and related conditions   |
| 8. Use steroids, protease inhibitors or antipsychotics (all of which have major effects on glucose metabolism and body fat distribution)       |
| 9. Current oral hypoglycaemic use                                                                                                              |
| 10. Symptomatic IBS                                                                                                                            |
| 11. History of renal or liver diseases                                                                                                         |
| 12. History of clotting or bleeding disorders                                                                                                  |
| 13. Taken antibiotics in last 3 weeks prior to screening                                                                                       |
| 14. Taking daily medications or dietary supplements that are not suitable for the study in the opinion of the PI                               |
| 15. Anaemia                                                                                                                                    |
| 16. Subject to a major medical or surgical event requiring hospitalization within the preceding 3 months                                       |
| 17. Current participation in another clinical study.                                                                                           |

**Table 2 Summary of MULBERRY trial schedule**

|                                             | Screening Visit | Visit 1 | Visit 2 | Visit 3 | Visit 4 |
|---------------------------------------------|-----------------|---------|---------|---------|---------|
| Informed Consent                            | •               |         |         |         |         |
| Demographic Info (age, contact details etc) | •               |         |         |         |         |
| Medical History                             | •               |         |         |         |         |
| Inclusion/Exclusion Criteria                | •               |         |         |         |         |
| Compliance Check (fasting, drugs etc)       |                 | •       | •       | •       | •       |
| Physical Exam (BMI, waist circ. etc)        |                 | •       | •       | •       | •       |
| Consume product / placebo + drink           |                 | •       | •       | •       | •       |
| Finger-prick glucose & insulin testing      |                 | •       | •       | •       | •       |
| GI Questionnaire                            |                 | •       | •       | •       | •       |
| Adverse Event Monitoring                    |                 | •       | •       | •       | •       |
